**6.3 Daily aTBS sessions.** All study subjects will receive 30 sessions of sequential bilateral aTBS or sham stimulation. The research team will use the Beam F3 method for coil localization of the RDPFC and LDPFC. Prior studies have demonstrated the validity and reliability of the Beam F3 method for coil localization in comparison to magnetic resonance guided approaches. Prior work demonstrated that the Beam F3 method is a feasible, valid, and reliable method for coil localization for TMS protocols in adolescents. Subjects in the active arm will receive 11.5 minutes sessions of sequential bilateral aTBS at 80% active MT, 3 times daily (1 hour apart) for 10 days in total (5 days per week). Each session includes TBS in which 1800 pulses are delivered continuously over 120 seconds to RDPFC followed by iTBS in which 1800 pulses are delivered in 2 second bursts, repeated every 10 seconds for 570 seconds (1800 pulses) to the LDPFC. Subjects assigned to the sham arm will receive identical treatment but with a magnetic field strength less than 5% of the active treatment. The stimulation parameters proposed here are adapted from initial work with adolescents and previously published clinical trial literature, showing that bilateral accelerated TBS is both feasible and safe for patients. Broadly, theta burst stimulation is delivered with 3-pulse 50 Hz bursts given every 200 ms (at 5 Hz) with an intensity of 80% of active MT. The MagVenture TMS Therapy System will be used in accordance with a FDA investigational device exemption (IDE). The device consists of a magnetic stimulator, MagPro X100 with MagOption and two magnetic coils. The C-B70 coil is for MT determination. The Cool-B70 A/P coil is the treatment coil. The Cool-B70 A/P coil that will be used was specifically designed for double-blind, sham-controlled trials. The coil contains both an active site (A) and a sham site (P). The active site is identical to a previously FDA cleared standard coil, Cool-B70 in terms of magnetic field properties. The sham site has a significantly reduced magnetic field, which is less than 5% of that of the active site, enabling a sham stimulation. As the coil contains both an active and a sham site, it is possible to blind the operator as well, as the coil looks identical on both sites. The coil has somatosensory electrodes to enhance the blinding of participants and operators. The electrodes are placed on the RDPFC and LDPFC under the coil during stimulation. The keeping of the blind is dependent on the use of a dedicated coil for MT determination. The C-B70 coil will be used for MT determination. The C-B70 coil is identical in terms of magnetic properties to the Cool-B70 A/P coil, but is a lightweight, non-cooled coil.

**Concurrent Psychotherapeutic Sessions .** All subjects will receive psychotherapeutic treatment which meets and exceeds the local standard of care. This will consist of daily psychotherapeutic sessions during the 10-day course of sequential bilateral aTBS or sham treatment. The psychotherapeutic treatment protocol was adapted from prior NIMH funded work and a grant funded intensive outpatient program at UT Southwestern Medical Center Dallas. [name] (consultant) assisted in the proposed adaptation and will provide ongoing input to [name]. [name] will provide local supervision and oversight of the 10-day psychotherapy program. The research team will collect information on subsequent psychotherapy treatments during the 1-year follow up period.

## 6.4 Methods and Measures

Table 4 describes the assessments for the study.

| Table 4. Description of Assessments                                                                                                            |                                                                                                                                                                                                                                                                                                                                                                 |
|------------------------------------------------------------------------------------------------------------------------------------------------|-----------------------------------------------------------------------------------------------------------------------------------------------------------------------------------------------------------------------------------------------------------------------------------------------------------------------------------------------------------------|
| Assessment                                                                                                                                     | Description                                                                                                                                                                                                                                                                                                                                                     |
| Antidepressant Treatment History Form (ATHF)                                                                                                   | Collected at baseline to systematically document prior psychotropic medication exposure and for quantification of treatment resistance (number of failed antidepressant trials with an adequate dose and duration).                                                                                                                               |
| Adverse events                                                                                                                                 | Subjects will be evaluated for adverse events at each visit. Serious adverse events (SAEs) will be reported as they occur to the Mayo Clinic IRB and USA FDA (as per regulations). Systematic data collection focused on adverse events will include the Pediatric Adverse Event Rating Scale and Physical Symptom Checklist.                |
| Auditory thresholds                                                                                                                            | Subjects will undergo audiometry testing at baseline and upon completion of 10 days of sequential bilateral aTBS.                                                                                                                                                                                                                                               |
| Beck Depression Inventory-II                                                                                                                   | This is a validated, 21-item, self-report measure with a range of 0-63. Collected at screening, baseline, weekly during the 10-day treatment and then monthly for 1 year follow-up period.                                                                                                                                                        |
| Brief Affective Neuroscience Personality Scale                                                                                                 | This is a validated 33-item, self-report measure collected at screening only to assess behavioral characteristics in 6 affective neurobiological systems (play, seek, care, fear, anger, and sadness)                                                                                                                                                           |
| CDRS-R – Childhood Depression Rating Scale – Revised                                                                                           | This is a validated, 17-item, clinician-rated tool to assess severity of depression. Parents provide input into 14 of the items. Total possible scores range from 17 to 113. Collected at screening, baseline, and weekly (after 5 treatments and posttreatment) during 10-day treatment and then monthly for 1 year follow-up period.            |
| CGI-S– Clinical Global Impressions Severity Scale                                                                                              | A standard measure of symptom severity and treatment response. Collected at screening, baseline, weekly (after 5 treatments and posttreatment) during 10-day treatment and then monthly for 1 year follow-up period.                                                                                                                              |
| C-SSRS – Columbia Suicide Severity Rating Scale                                                                                                | This is a validated, clinician-rated tool collected to assess lifetime and ongoing suicidal ideation and behavior at screening, baseline, daily during the 10 day treatment, then monthly for 1 year follow-up period. The severity of ideation subscale is a 5-point ordinal scale that is the primary clinical outcome measure for this study.  |
| Demographics Questionnaire                                                                                                                     | This is a self-reported questionnaire that collects the subjects gender, race, ethnicity, sexual orientation and educational levels of parents.                                                                                                                                                                                                                 |
| Mini-International Neuropsychiatric Interview for Children and Adolescents (MINI Kid) and Mini-International Neuropsychiatric Interview (MINI) | A structured psychiatric interview (MINI Kid for ages 12-17 and MINI for age 18 and). Collected at baseline to confirm diagnostic inclusion criteria and rule out diagnostic exclusion criteria.                                                                                                                                             |

|                                                                                      |                                                                                                                                                                                                                                                                                                                                                                                                                                                                                                                                                                                                                                                                                                                                                                                                                                                                                                                                                                                                                                                            |
|--------------------------------------------------------------------------------------|------------------------------------------------------------------------------------------------------------------------------------------------------------------------------------------------------------------------------------------------------------------------------------------------------------------------------------------------------------------------------------------------------------------------------------------------------------------------------------------------------------------------------------------------------------------------------------------------------------------------------------------------------------------------------------------------------------------------------------------------------------------------------------------------------------------------------------------------------------------------------------------------------------------------------------------------------------------------------------------------------------------------------------------------------------|
| NIH Toolbox Cognition Battery                                                        | http://www.healthmeasures.net/index.php
Cognition measures: http://www.healthmeasures.net/explore-measurement-systems/nih-toolbox/intro-to-nih-toolbox/cognition
The NIH Toolbox Cognition Battery , recommended for ages 7+, consists of tests of multiple constructs. It yields individual measure scores and the following summary scores: Education, Handedness, Attention (Flanker Inhibitory Control and Attention Test), Episodic memory (Picture Sequence Memory Test, and Auditory Verbal Learning Test), Executive Function (Dimensional Change Card Sort Test, Flanker Inhibitory Control and Attention Test), Language (Picture Vocabulary Test, Oral Reading Recognition Test), Processing Speed (Pattern Comparison Processing Speed Test), Working Memory (List Sorting Working Memory Test). Collected at baseline and posttreatment.  |
| Pre/Post Treatment Expectations and Experience Questionnaire (Adolescent and Parent) | This questionnaire assesses patient and parent impressions, expectations, and the integrity of blinding by asking adolescents and parents to make a guess regarding study arm assignment. Collected at baseline and posttreatment.                                                                                                                                                                                                                                                                                                                                                                                                                                                                                                                                                                                                                                                                                                                                                                                                                         |
| Pubertal Development Scale and Tanner Staging                                        | A self-report questionnaire and line-drawings used to evaluate level of pubertal development. Collected at screening.                                                                                                                                                                                                                                                                                                                                                                                                                                                                                                                                                                                                                                                                                                                                                                                                                                                                                                                        |
| TASS – Transcranial Magnetic Stimulation Safety Screen                               | This safety screen is completed prior to TMS for confirmation patient safety. Collected at baseline.                                                                                                                                                                                                                                                                                                                                                                                                                                                                                                                                                                                                                                                                                                                                                                                                                                                                                                                                         |
| Vital Signs                                                                          | (Pulse, blood pressure, temperature, height, and weight) will be collected at screening and posttreatment.                                                                                                                                                                                                                                                                                                                                                                                                                                                                                                                                                                                                                                                                                                                                                                                                                                                                                                                                                 |
| YMRS-Young Mania Rating Scale                                                        | This is an 11-item measure used to assess for manic symptoms. The YMRS scale will be completed at baseline and repeated during the course of study participation if symptoms of mania occur in a study subject. If the YMRS is positive, A MINI/MINI-Kid will be repeated to evaluate for mania. If the study subject meets full DSM-5 criteria for mania or hypomania he or she will be discontinued from the study and followed clinically.                                                                                                                                                                                                                                                                                                                                                                                                                                                                                                                                                                                                |
| TMS Neurophysiology Measures                                                         | TMS-EMG (LICI-100) and TMS-EEG (LICI-100 and N100) neurophysiology measures will be collected in adolescent subjects at baseline and after the final day of sequential bilateral aTBS.
25, 81                                                                                                                                                                                                                                                                                                                                                                                                                                                                                                                                                                                                                                                                                                                                                                                                                                                           |

**Clinical and Standardized Assessments:** At screening subjects will undergo a urine drug screen, urine pregnancy test, MINI-Kid or MINI interview, Brief Affective Neuroscience Personality Scale, CDRS-R, C-SSRS, Childhood Trauma Questionnaire, Clinical Global Impressions Scale (CGI), Safety Screening for TMS, Young Mania Rating Scale, Adverse Event Rating Scales, Medical History, Physical Exam, Vital Signs, Pubertal Development Scale, and the Beck Depression Inventory-II (BDI-II). At the baseline visit subjects will repeat the CDRS-R, C-SSRS, CGI, BDI-II, and Adverse Rating Scales. Other baseline assessments include the NIH Toolbox Cognition Battery, Auditory Threshold Testing, and a Pre-treatment Expectation and Experience Questionnaire. Subjects will undergo TMS-EMG testing and TMS-EEG testing at the baseline line visit. The C-SSRS (suicidal ideation severity subscale, which is the primary outcome measure) will be assessed daily for the 10 treatment days. The CDRS-R, CGI, and BDI-II will be collected weekly during the treat period (baseline, after 5 treatments, and posttreatment). After the final day of treatment, the subjects will complete the C-SSRS, CDRS-R, CGI, BDI-II, Post-treatment Expectation and Experience Questionnaire and the NIH Toolbox Cognition Battery. Vital signs will be collected at this posttreatment visit. Subjects will undergo posttreatment TMS-EMG and TMS-EEG testing. Follow-up, post-treatment assessments will be collected each month over the 12-month follow-up period. These monthly assessments will include the C-SSRS, CDRS-R, CGI, BDI-II, number of hospitalizations related to suicidality, and number of emergency department visits

related to suicidality. Concurrent medications, concurrent psychotherapy, and adverse events will be collected at every study visit.

**Neurophysiological TMS:** Neurophysiological TMS procedures (LICI-100 is the primary outcome measure) will be conducted at Mayo Clinic with our standard protocols that have been published previously. Relaxation will be monitored with audio feedback. Surface EMG readings are collected from the abductor pollicis brevis (APB) muscle. The TMS-EMG panel includes LICI, SICI, intracortical facilitation (ICF), and the cortical silent period (CSP) counterbalanced to avoid order effects. Note that SICI, ICF, and CSP are collected for exploratory analyses and are not the focus of the present grant specific aims. The primary outcome measure is LICI-100 (LICI with an ISI of 100 ms). The TMS-EEG recordings (for LICI-100 and N100 as examined in prior studies of adults) will be acquired through a 64-Channel EEG (EGI Foundation) System in accordance with prior published protocols (that have yielded high test-retest reliability with an intraclass correlation coefficient greater than 0.9). In light of recent controversies and publications, the protocol will include a realistic sham (scalp and auditory stimulation) to account for peripheral multisensory stimulation. A foam sponge will be placed between the coil and the EEG cap to reduce tactile artifact. Foam earphones and white noise cancellation will be used to mask the auditory click that occurs with TMS, thereby mitigating auditory artifact.

**TMS-EMG:** The research team will ensure participants maintain relaxation during the procedures with audio feedback tests. TMS stimulation will be applied to the hand area of the contralateral cortex with a figure-of-eight magnetic coil (with a coil diameter of 70 mm on each loop) using the Magstim 200 magnetic stimulator device. The resting MT is defined as the stimulation intensity which elicits a motor evoked potential (MEP) of > 50 microvolts in 5 of 10 trials with a relaxed APB muscle. For LICI measurements, a suprathreshold conditioning stimulus (CS) precedes a suprathreshold test stimulus (TS). The CS and TS are both set to 120% of resting MT, which is calibrated to produce an average MEP of 0.5 to 1.5 millivolt peak-to-peak amplitude in the contralateral APB muscle. Conditioning stimuli are delivered to the motor cortex prior to the TS in one of three random ISIs at 100 ms, 150 ms, and 200 ms along with single TS randomly interspersed within the three random ISIs. Changes in TS MEP amplitude of each ISI are expressed as a percentage of the mean unconditioned MEP amplitude.

**TMS-EEG:** TMS-EEG data for the exploratory aim will be collected with standard procedures published previously. Subjects will undergo LICI-100, N45, and N100 in the LDPFC with a 64-Channel EEG (EGI Foundation), TMS compatible MicroCel net in place. The research team will ensure participants maintain relaxation during the procedures with audio feedback tests. TMS stimulation will be applied to the hand area of the contralateral cortex with a figure-of-eight magnetic coil (with a coil diameter of 70 mm on each loop) using the Magstim 200 magnetic stimulator device. The TMS coil is held tangentially on the head with the handle backward at 45 degrees laterally from the midline to determine resting MT. The optimal coil position is located by moving the coil in 1-cm increments over the motor cortex. The resting MT is defined as the stimulation intensity which elicits a motor evoked potential (MEP) of > 50 microvolts in 5 of 10 trials with a relaxed APB muscle. For DLPFC stimulation, the TMS coil is localized over the F5 electrode in line with AF3. This approach has been shown to yield quality data in adults and magnetic resonance guided localization is not practical in the context of this exploratory work. The EEG electrodes will be referenced to Cz. In line with recent

collaborative efforts to improve the validity and reliability of TMS-EEG biomarkers, data collection will include a realistic sham condition (scalp and auditory stimulation). These measures will ensure the appreciation of sensory event-related potentials and related impact on TMS-EEG N45 and N100 recordings. Recordings will be in DC mode with 1000-Hz low pass filter (48 dB/octave) and a sampling rate of 20 kHz. These recording parameters have been shown to avoid amplifier saturation and minimize TMS-related artifact.

For LICI measurements, a suprathreshold conditioning stimulus (CS) precedes a suprathreshold test stimulus (TS). The CS and TS are both set to 120% of resting MT, which is calibrated to produce an average MEP of 0.5 to 1.5 millivolt peak-to-peak amplitude in the contralateral APB muscle. Conditioning stimuli are delivered to the motor cortex prior to the TS in one of three random ISIs at 100 ms, 150 ms, and 200 ms along with a single TS randomly interspersed within the three random ISIs. Changes in TS MEP amplitude of each ISI are expressed as a percentage of the mean unconditioned MEP amplitude. For N100 response data collection, mean single pulse data will be collected for each electrode for the TMS-evoked potential. The N100 peak value is then extracted throughout electrodes from the negative in closest proximity to 100 ms.

Custom MATLAB scripts and EEGLAB toolbox will be used for EEG preprocessing. The EEG signal will be resampled from 20 kHz to 1000 Hz and epoched into trials with data from 1000 ms before to 1000 ms after the onset of each test pulse. Artifact free periods will be used to baseline correct and remove TMS artifact. Channels and trials with amplitude and frequency outliers will be removed. Independent component analyses will be applied to the data. Components with TMS decay artifacts will be removed. The signal will be band-pass filtered to the range of physiologically meaningful EEG (1-80 Hz) along with a notch filter set to 60 Hz to remove line noise. Other outlier trials and channels will be removed with a second independent component analysis to remove eye blinks, electrode artifacts, muscle artifacts, and sensory artifacts. Missing channels will be interpolated with linear surface interpolation. All channels will be average referenced.

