## **Exploratory Aim**

### **Data Analysis Plan for Exploratory Aim 3 (Hypotheses 3a–3b)**

#### Exploratory Ordinal Outcome for Aim 3: Suicidal Ideation at Baseline Period

**Hypothesis 3a:** We expect that cortical inhibition (as assessed by pre-treatment LIC1-100 and N100 collected with TMS-EEG) will have an indirect relationship with severity of suicidal ideation (as assessed by the C-SSRS severity of ideation subscale) in all participants at baseline.

An ordinal logistic regression model similar to that described above for Hypothesis 2a will be used to estimate severity of suicidal ideation at baseline from baseline measures of LIC1-100 and N100. A separate model will be implemented for each measure of TMS-EEG cortical inhibition. The same covariates specified in Hypothesis 2a will be included in the model for Hypothesis 3a. The adjusted odds ratios (i.e., odds of suicidal ideation from LIC1-100 and N100), and 95% confidence interval, will be estimated as part of the model so as to interpret the relationship between each TMS-EEG biomarker and baseline suicidal ideation.

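### The TMS-EEG text in Section 6.4 contradicts itself on LICI-100: it is placed in the left DLPFC with EEG but defined by motor-cortex pulses and hand-muscle MEPs

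*Protocol*

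**What the plan says.** The TMS-EEG part of Protocol Section 6.4 opens by placing the measures in the prefrontal cortex: "Subjects will undergo LICI-100, N45, and N100 in the LDPFC with a 64-Channel EEG (EGI Foundation), TMS compatible MicroCel net in place". It also gives a coil position for that site: "For DLPFC stimulation, the TMS coil is localized over the F5 electrode in line with AF3".

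A later paragraph of the same TMS-EEG text defines LICI. The pulse intensity is one "which is calibrated to produce an average MEP of 0.5 to 1.5 millivolt peak-to-peak amplitude in the contralateral APB muscle". On site and intervals, all in milliseconds, it says: "Conditioning stimuli are delivered to the motor cortex prior to the TS in one of three random ISIs at 100 ms, 150 ms, and 200". The read-out is: "Changes in TS MEP amplitude of each ISI are expressed as a percentage of the mean unconditioned MEP amplitude".

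The TMS-EMG part of Section 6.4 uses the same sentences to define TMS-EMG LICI, the biomarker of secondary Aim 2.

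Section 7.2 uses TMS-EEG LICI-100 as a predictor in the analysis of Hypothesis 3a and in the model paragraph of Hypothesis 3b. For 3a, and in the same terms for 3b, it states: "A separate model will be implemented for each measure of TMS-EEG cortical inhibition".

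**The concern.** A motor evoked potential is a muscle response. Section 1.4 describes it as evoked by a pulse to the motor cortex and recorded from the hand. A ratio of MEP amplitudes is therefore an EMG quantity from the motor system and contains nothing from the 64 EEG channels. Sections 1.1 and 2 justify TMS-EEG on the ground that it may reflect prefrontal inhibition more directly than EMG does. The definition as written does not deliver that.

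The stimulation site matters more than the scoring rule. A wrong scoring rule can be corrected at analysis if the EEG was recorded with prefrontal paired pulses. If operators followed the motor-cortex wording, prefrontal paired-pulse data would not exist and no later analysis could recover them.

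**Working it through.** The protocol gives no figure to reproduce here. The check is a comparison of texts, followed by tracing the measure into the analysis.

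**1. The two LICI definitions in Section 6.4, element by element**

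| Element | TMS-EMG text | TMS-EEG text, LICI paragraph | TMS-EEG text, elsewhere |
|---|---|---|---|
| Site | motor cortex | motor cortex | left DLPFC, coil over F5 in line with AF3 |
| Intensity | 120% of resting MT, calibrated to an APB MEP | the same | not stated |
| Intervals | 100, 150, 200 ms | the same | not stated |
| Read-out | MEP amplitude | MEP amplitude | 64-channel EEG |
| Scaling | percent of mean unconditioned MEP | the same | not stated |

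The four-sentence definition has 102 words in the EMG text and 103 in the EEG text. The only difference is an inserted indefinite article. The word-level similarity is 2 × 102 / (102 + 103) = 204/205 = 0.995.

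**2. Is an EEG read-out for LICI given elsewhere?** No.
- N100, in the sentences directly after the LICI paragraph, has an EEG read-out: the single-pulse evoked potential at each electrode.
- The preprocessing paragraph cuts EEG epochs around each test pulse, filters and re-references them, but derives no LICI value.
- Tables 3 and 4 only name the measure.
- The neurophysiology overview in Section 6.4 refers to published protocols without giving their content.

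**3. Where the measure enters the analysis (Section 7.2)**
- Hypothesis 3a: ordinal logistic model at baseline, all participants, same outcome and covariates as Hypothesis 2a.
- Hypothesis 3b: GEE ordinal model in the active arm, same outcome and covariates as Hypothesis 2b.
- Each is fitted once for LICI-100 and once for N100: 2 hypotheses × 2 measures = 4 models, of which 2 use LICI-100.

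Under the literal definition, those 2 models have the same outcome, population, covariates and predictor construct as 2a and 2b.

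**4. The biomarker list for 3b.** The exploratory objective in Section 2.2, the endpoint in Section 3.3 and the wording of Hypothesis 3b name N45 and N100. The model paragraph for 3b names LICI-100 and N100. So LICI-100 is modelled there without being hypothesised, and N45 is hypothesised without being modelled.

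**The case against.** The best defence is that the intent is clear. The TMS-EEG text opens with the left DLPFC and a prefrontal coil position. The neurophysiology overview assigns LICI-100 to the 64-channel system and follows published protocols, one of which is listed in the references as a TMS-EEG study of long-interval inhibition from that region. The EEG epochs are centred on test pulses, a paired-pulse term. An experienced laboratory would probably record the right thing. Electrodes, time window and the exact EEG ratio for an exploratory biomarker may also properly sit in the SAP or a laboratory procedure, neither of which is shown.

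Most of this stands. It establishes the intent, and it means that the absence of a full EEG formula is not by itself a defect of the protocol. It does not remove the conflict. A general reference to published methods does not override specific contrary text, and an SAP cannot repair an acquisition instruction that names the wrong site.

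Three stronger readings are tempting, and the documents do not support them:

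- A reader might infer that prefrontal EEG inhibition will not be measured at all. That follows only if the LICI paragraph is read alone. The same section plans prefrontal EEG recording, and N100 has a proper EEG read-out.
- A reader might infer that EMG and EEG LICI would be the same number. Even on the literal text, a separate recording run gives a repeat measurement of one construct, not an identical value.
- A reader might infer that agreement between the two will be presented as independent confirmation. The protocol plans no concordance analysis, so this would be a risk of interpretation only.

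**Conclusion.** The point holds as an internal contradiction. Within the TMS-EEG text of Section 6.4, the stated site and modality of LICI-100 conflict with its only operational definition, which is the TMS-EMG paragraph left unadapted. Followed literally, that paragraph would make the LICI-100 predictor in two of the four TMS-EEG models a repeat of the motor-cortex MEP construct of Aim 2.

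The consequence is small. Only the exploratory aim is touched; Hypothesis 1a, TMS-EMG LICI under Aim 2 and the sample size are unaffected. The practical effect depends on something the protocol does not settle: whether paired pulses are in fact delivered at the prefrontal site. If they are, only text is wrong. If they are not, the recording itself departs from the stated purpose.

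**What to change.** 1. Rewrite the LICI paragraph in the TMS-EEG text. Paired pulses are delivered at the left DLPFC site already described there, and LICI-100 is the conditioned TMS-evoked EEG response relative to the unconditioned one. Electrodes and time window may be set in the SAP or a laboratory procedure, provided they are fixed before the data are analysed.
2. Keep the MEP rule for TMS-EMG only.
3. Ask the sponsor to confirm that prefrontal paired-pulse recording is what is performed. If it is not, either change the acquisition or drop TMS-EEG LICI-100 from 3a and 3b.
4. Align the biomarkers for Hypothesis 3b across Sections 2.2, 3.3 and 7.2, so that those hypothesised are those modelled.

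The cost is about one paragraph of measurement text plus the aligned list. No new recording is needed if step 3 confirms the prefrontal acquisition.
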